#### Intervention feasibility

2.3.1

To address scheduling challenges and classroom disruptions in MOVE12, the implementation of MOVE-breaks was designed with flexibility to accommodate the unique traditions, practices, and challenges of individual schools and classes. This collaborative approach, grounded in research-based strategies, promotes effective integration into diverse educational settings. The study design incorporates peer-led sessions (Table 2), where student pairs co-lead MOVE-breaks to foster autonomy, reduce teacher workload, and enhance peer accountability while maintaining classroom order (33, 53). Integration into the curriculum, such as fixed 10-min breaks during natural transitions in 90-min lectures, minimizes disruptions and optimizes participation (49). Classroom management protocols, including clear guidelines, designated movement areas, and student role assignments, maintain structure and discipline during activities (50). Regular feedback mechanisms will gather input from teachers and students on scheduling preferences and activity formats, enabling iterative refinements to improve feasibility and satisfaction (51). Lastly, providing simple, minimal equipment, such as portable items like beanbags or dice, ensures activities are quickly initiated and cleared, minimizing logistical hurdles and interruptions. These strategies collectively enhance the adaptability, effectiveness, and sustainability of MOVE12 across varied school contexts.

#### Stakeholder engagement

2.3.2

To ensure the sustainability of MOVE12, stakeholder engagement (Table 2) will be a critical factor. Following the conclusion of MOVE12, a subsequent main intervention is planned, which will maintain the involvement of the same teacher ambassadors. Together with school leaders and additional teachers recruited for the main intervention, these stakeholders will receive close follow-up through regular meetings with the project leadership, both prior to and during the intervention period. After the main intervention, the project leader will establish ongoing collaboration by organizing periodic meetings with school leaders and teacher ambassadors, facilitated by the county municipality. These meetings aim to sustain engagement, share experiences, and develop strategies for integrating the intervention into long-term school routines.

### Program production

2.4

Building on the methodologies and applications selected in Step 3, the fourth step of the IM protocol process entails the development of the intervention program, complemented by a detailed inventory of materials necessary for execution. The program production is divided into two primary phases:

#### Preparation phase

2.4.1

This initial phase is dedicated to applying the findings from the previous theoretically based steps by developing a strategy to promote the initiative among students and teachers, and by preparing presentations and relevant tools/materials for the planned intervention. Distinct 60-min information sessions will be conducted for school leaders, teachers, and students to ensure each participant is thoroughly briefed on their roles and responsibilities. For these sessions, a PowerPoint presentation will be prepared, detailing the program's rationale, objectives, content, outcomes, and ethical considerations. Moreover, students will receive details on the MOVE-breaks, explaining its incorporation into a specific competency goal in physical education that requires planning, executing, and evaluating a personal training period. Additionally, a 5-min demonstration video showcasing various physical measurement techniques will be created for students. For teachers, we will create a promotional video lasting 5 min that emphasizes the benefits of incorporating brief MOVE-breaks into classroom settings (54).

#### Practice phase

2.4.2

The next phase focuses on giving students practical-methodological practice in various ways to conduct MOVE-break sessions. It includes two 90-min sessions where students, in pairs, use the exercise compendium as a reference to plan, conduct, and assess their own 6–7-min MOVE-breaks for their peers, under the guidance of the physical education teacher. These practice sessions can be held in classrooms or suitable indoor/outdoor spaces nearby.

### Program implementation plan

2.5

The fifth step of the IM protocol process focused on planning the adoption, implementation, and sustainability of the intervention. This stage emphasizes engaging stakeholders to address barriers and refine strategies to maximize the intervention's reach and impact. Stakeholder discussions played a pivotal role in shaping the implementation plan. For example, feedback from school leaders and teacher ambassadors highlighted the need for financial incentives to encourage teacher ambassadors' active involvement. This input led to the allocation of dedicated funding to support their roles, ensuring consistent oversight and motivation during the intervention. Additionally, the needs assessment highlighted the importance of tailored communication strategies for parents to foster engagement and extend the program's impact beyond the classroom. In response, an information letter was developed to emphasize the benefits of MOVE-breaks in enhancing students' physical activity levels and overall well-being. As illustrated in Figure 3, the implementation of MOVE-breaks commenced following the completion of baseline measurements at the end of January 2023 and continued for a 12-week period, concluding in April 2023. This timeline allowed for a structured rollout while maintaining flexibility to address any unforeseen challenges. By incorporating the iterative refinements, the implementation plan was aligned with the practical needs of schools and stakeholders, enhancing the likelihood of sustained adoption and success.

**Figure 3 F3:**
[figure not shown]
Timeline for the MOVE12 pilot intervention study.

#### Study design

2.5.1

This protocol paper, developed using the intervention mapping (IM) framework, describes the planning of a 12-week cluster-randomized mixed-methods pilot study, incorporating both quantitative and qualitative data collection and analysis. The target population included first-year upper secondary school students from a broad region in southeastern Norway (three counties), aiming for balanced representation of academic and vocational programs. Invitations were sent to 27 upper secondary schools, and five agreed to participate (three academic, two vocational). One vocational school, twice the size of the others, contributed approximately 200 students, while each of the remaining four contributed about 100 students. Of 739 eligible students, 519 provided consent. The inclusion criteria for participation were students aged 16–17 years, with exclusion criteria defined as disabilities preventing participation and/or illnesses posing health risks.

#### Randomization procedure

2.5.2

The MOVE12-pilot study was designed as a two-arm, three-level cluster randomized controlled trial (RCT), featuring an intervention group (IG) and a control group (CG), with participants organized within classrooms and schools. Participants were randomly assigned to either the IG or the CG (1:1) by the principal investigator (PI). At the three academic schools (class size: 25–30), four relatively homogeneous classes were identified, and randomization involved drawing from two boxes (one for group assignment, one for classes) in alternating turns until all classes were assigned. At the two vocational schools (class size: 12–17), classes were stratified by gender, size, and subject area before following the same procedure using four boxes (A–D). Twice as many groups were drawn from the vocational school that was double the size of the others.

#### Intervention content

2.5.3

During the intervention period, the intervention groups were encouraged to incorporate at least two 6–7-min MOVE-breaks into their daily classroom sessions. The PE teacher, in collaboration with the participating teachers, coordinated the rotation of student pairs responsible for leading these sessions in various lectures. Additionally, teacher ambassadors played a crucial role in assisting with the implementation of the intervention. They worked closely with the Principal Investigator (PI) to provide support and encouragement to both the teachers and participating students. To support this process, the project team developed a digital activity guide featuring strength- and endurance-based exercises for the classroom. Students created their own MOVE-break session plans, adding images and descriptions. They also used computers to play follow-along dance videos (e.g., “Just Dance”) via the classroom projector. In addition, each class received simple equipment (beanbags, cards, dice) for basic games, team exercises, and relay activities.

### Evaluation plan

2.6

The aim of MOVE12 is to increase students' physical activity levels in school through participation in 1–2 daily MOVE-breaks lasting 6–7 min each. This goal is pursued by enhancing their knowledge, fostering positive attitudes, boosting self-esteem, and nurturing intrinsic motivation at the individual level, while also focusing on providing opportunities and social support from teachers and peers (see Table 1). The findings from our planned evaluation will be reported in accordance with the CONSORT 2010 guidelines for randomized trials (55).

#### Primary outcome measures

2.6.1

The primary outcome measures align with the study's core objective: promoting student participation in 1–2 daily MOVE-breaks (6–7 min each) during regular class sessions (Table 1). Feasibility and implementation will be assessed by evaluating students' adherence to MOVE-breaks and gathering insights into the subjective experiences of both students and teachers. These evaluations will be guided by changeable determinants such as knowledge, attitude, self-efficacy, basic psychological needs (autonomy, competence, relatedness), social support, school culture, and the physical environment. Data will be collected through focus group discussions at the 12-week follow-up, providing a comprehensive understanding of the intervention's effectiveness.

#### Secondary outcome measures

2.6.2

Additionally, the study aims to evaluate potential effects of MOVE-breaks on physical fitness, psychosocial health parameters, and school-related factors through the following outcome measures:
-Attention and Concentration: Measured with the Eriksen Flanker Test (56) and the Stroop Test (57) before and after a designated MOVE-break session at the midpoint of the intervention.-Heart Rate Measurements: Measured during a designated MOVE-break session at the midpoint of the intervention using the Polar Team Pro System (58).-Physical Activity Level: Measured using the ActiGraph wGT3X-BT (59) at baseline and 12-week follow-up.-Aerobic Fitness: Measured with the YMCA 3-min step test (60) at baseline and 12-week follow-up.-Muscle Strength: Measured by (i) standing long jump (61) and ii) handgrip (dynamometer) (62) at baseline and 12-week follow-up.-Postural Balance: Measured by two-leg standing, eyes closed (30 s) and one-leg standing, eyes open (30 s) (63) at baseline and 12-week follow-up.-Flexibility: Measured by the sit-and-reach test (64) at baseline and 12-week follow-up.-Sleep Quality: Measured by an online questionnaire (Nettskjema.no) at baseline and 12-week follow-up using four single items from a modified version of the Karolinska Sleep Questionnaire (65).-Wellbeing: Measured by an online questionnaire (Nettskjema.no) at baseline and 12-week follow-up using the Warwick-Edinburgh Mental Wellbeing 7-item scale (66).-Self-Efficacy: Measured by an online questionnaire (Nettskjema.no) at baseline and 12-week follow-up using a factor developed by Sørlie and Nordahl (67), based on Bandura (68).-Learning Environment and Social Wellbeing in Class: Measured by an online questionnaire (Nettskjema.no) at baseline and 12-week follow-up using 13 items developed by Moos and Trickett (69), translated and processed by Sørlie and Nordahl (67).-Social Isolation: Measured by an online questionnaire (Nettskjema.no) at baseline and 12-week follow-up using 21 items from the Social Skills Rating System by Gresham and Elliott (70), translated and processed by Sørlie and Nordahl (67).

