### Quantitative and qualitative data analysis

2.7

Data analysis will combine quantitative and qualitative approaches. To examine between-group differences in continuous outcome measures from baseline to the 12-week follow-up, a linear mixed model (LMM) will be applied. LMM addresses the nested data structure of MOVE12 (students within classrooms, classrooms within schools) by incorporating random intercepts to account for intra-class correlation and hierarchical clustering effects (71). Additionally, LMMs handle missing data robustly under the assumption of missing at random (72), a common scenario in school-based interventions. Within-group changes will be assessed using dependent *t*-tests, and potential associations between ordinal outcome measures will be explored through multiple and binary regression analyses. All statistical analyses will be conducted using STATA version 18.0 (73).

Qualitative methods will be used to identify key themes from the planned focus group interviews, guided by determinants such as knowledge, attitude, self-efficacy, basic psychological needs (autonomy, competence, relatedness), social support, school culture, and the physical environment. This qualitative approach aims to deepen our understanding of how these factors influence participants' experiences and engagement with the intervention, thereby informing both practical implementation and theoretical implications. Qualitative data will be analyzed thematically using NVivo 14 software to support and manage the analytic process (74).

*a priori* sample size calculations with G-Power (75) suggested that a sample of 580 participants would be sufficient to detect a moderate effect size (*d* = 0.3), assuming a two-group design, 80% power, and an alpha of.05.

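### The midpoint attention tests have no described comparator, and the only stated analysis that fits them cannot separate a MOVE-break effect from retest practice or other within-session change

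*Protocol article*

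**What the plan says.** All places are in the protocol article.

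- **Secondary outcome measures (2.6.2).** The stated purpose is causal: "the study aims to evaluate potential effects of MOVE-breaks on physical fitness, psychosocial health parameters, and school-related factors". Attention and concentration are assessed with the Flanker and Stroop tests "before and after a designated MOVE-break session at the midpoint of the intervention". No baseline or 12-week measurement of attention is listed. The only other midpoint measure is heart rate, recorded during the break. The remaining outcomes are taken at baseline and 12 weeks.
- **Intervention content (2.5.3).** MOVE-breaks belong to one arm: "the intervention groups were encouraged to incorporate at least two" of them each day.
- **Randomization procedure (2.5.2).** The trial has a randomised comparator, "featuring an intervention group (IG) and a control group (CG", allocated 1:1. No role is described for it in the attention test.
- **Quantitative and qualitative data analysis (2.7).** "To examine between-group differences in continuous outcome measures from baseline to the 12-week follow-up, a linear mixed model (LMM) will be applied". For change inside an arm: "Within-group changes will be assessed using dependent" t-tests. The regressions in the same paragraph are for associations between ordinal outcomes.

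**The concern.** The test pair is tied to an event that only the intervention arm is asked to have, and the randomised comparison is written for time points at which attention is not measured. As described, the trial's control group does no work for this outcome. A before-after change in one arm adds together the effect of the break and everything else that alters a second test score minutes after the first: familiarity with the task, time elapsed in the lesson, fatigue, and students' expectation that the break should help.

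The outcome is nevertheless listed as evidence on effects of MOVE-breaks. The section on theory-based intervention methods (2.3) also names better concentration among the benefits to be demonstrated when policymakers review programme data. It does not tie that claim to these two tests, but they are the only quantitative attention measures in the article. A significant paired test could be carried forward as an effect of the break when the design cannot show one.

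**Working it through.** **1. Which stated analysis fits the data?**

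| Stated analysis | Scope given in 2.7 | Fits the midpoint pre/post pair? |
|---|---|---|
| Linear mixed model | Between-group, baseline to 12 weeks | No, attention is not measured at either time |
| Multiple and binary regression | Associations between ordinal outcomes | No |
| Dependent t-test | Within-group change | Yes |

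The dependent t-test remains, by elimination.

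**2. What does that test estimate?** Write b for the break effect and p for everything else that moves the second score (practice, time, fatigue, expectancy). The mean change in tested intervention classes is b + p. The paired test addresses b + p = 0, not b = 0. A control pair at the same interval would have mean change p, and the difference between arms would be (b + p) − p = b, for the part of p that is common to both arms. Expectancy that is specific to the break would not cancel.

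**3. How far could the test mislead?** The article gives no figure to reproduce on this point, so what follows is an illustration.

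Inputs:
- Number tested: not stated. Upper case: 519 consented (Study design, 2.5.1) at 1:1 gives 519 / 2 ≈ 260. Lower case: 100, assumed.
- True break effect: b = 0.
- Practice gain d: 0.10, 0.15 and 0.20 SD, assumed.
- Pre-post correlation r: 0.5 and 0.7, assumed.
- Two-sided alpha 0.05.

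Formulas: dz = d / √(2(1 − r)); noncentrality = dz × √n; rejection rate from the noncentral t on n − 1 degrees of freedom.

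Worked case: d = 0.10, r = 0.7 gives dz = 0.10 / √0.6 = 0.129. With n = 260 the noncentrality is 0.129 × 16.12 = 2.08 against a critical value of 1.969, and the test rejects in 55% of trials.

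| n | r | d = 0.10 | d = 0.15 | d = 0.20 |
|---|---|---|---|---|
| 260 | 0.5 | 36% | 67% | 89% |
| 260 | 0.7 | 55% | 88% | 99% |
| 100 | 0.5 | 17% | 32% | 51% |
| 100 | 0.7 | 25% | 48% | 72% |

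With a smaller shift, dz = 0.05, the rates are 13% (n = 260) and 8% (n = 100). Every entry exceeds the nominal 5%, and for a given shift a larger sample raises it.

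**The case against.** The strongest reply is that much of this is read from silence. The article gives the outcome one line, with instrument and timing. It does not say which classes were tested, and it does not link the paired t-test to Flanker or Stroop. A parallel control session, a familiarisation run or the test order could sit in a full protocol, and the timeline figure is not available here. A reader might infer that control classes were definitely not tested. The article does not say so, and that reading should not be adopted. What stands is narrower: the measurement as described is anchored to a break that only one arm is asked to hold, and the stated between-group model is written for other time points. That is a scheme the article sets out, not just a detail it leaves open.

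A reader might also infer that a positive result is close to certain even if the break does nothing. The figures do not support that. Only the upper part of the assumed range comes near certainty, and the lowest cases are 8% to 17%. The article does not say whether the score is speed, accuracy or an interference score, so the size of any practice gain is unknown, and fatigue could push the second score the other way.

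Finally, this is one secondary outcome in a pilot whose primary outcomes concern participation and implementation. That is correct, and it limits the grading.

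**Conclusion.** The point holds as a limit on interpretation. As described, the midpoint attention change cannot be attributed to the MOVE-break, because no comparator session is described and the one fitting analysis tests change from all causes together. If the break had no effect, the paired test would reject in about 36% to 99% of trials with 260 students and 17% to 72% with 100, for a practice gain of 0.10 to 0.20 SD and a correlation of 0.5 to 0.7. Those percentages rest on an assumed gain, correlation and number tested, none of which the article gives. The structural conclusion does not depend on them.

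Severity is minor. The primary feasibility outcomes and the outcomes compared from baseline to 12 weeks are unaffected.

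**What to change.** The program implementation plan (2.5) says the intervention ended in April 2023, so a control session can no longer be added to this pilot. What can be done depends on the data held:

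- **If control classes were tested at the same interval:** say so, and compare arms on the post-score adjusted for the pre-score, with a random intercept for class.
- **If they were not:** report the midpoint change descriptively, with no p-value and no statement that MOVE-breaks improve attention.
- **For the main intervention announced under Stakeholder engagement (2.3.2):** add a pre/post pair in control classes around ordinary seated lesson time, at the same interval.

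For the pilot, the cost is a more restricted claim on one secondary outcome. For the main intervention, it is one short test session per control class.

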### Quantitative and qualitative data analysis

2.7

Data analysis will combine quantitative and qualitative approaches. To examine between-group differences in continuous outcome measures from baseline to the 12-week follow-up, a linear mixed model (LMM) will be applied. LMM addresses the nested data structure of MOVE12 (students within classrooms, classrooms within schools) by incorporating random intercepts to account for intra-class correlation and hierarchical clustering effects (71). Additionally, LMMs handle missing data robustly under the assumption of missing at random (72), a common scenario in school-based interventions. Within-group changes will be assessed using dependent *t*-tests, and potential associations between ordinal outcome measures will be explored through multiple and binary regression analyses. All statistical analyses will be conducted using STATA version 18.0 (73).

Qualitative methods will be used to identify key themes from the planned focus group interviews, guided by determinants such as knowledge, attitude, self-efficacy, basic psychological needs (autonomy, competence, relatedness), social support, school culture, and the physical environment. This qualitative approach aims to deepen our understanding of how these factors influence participants' experiences and engagement with the intervention, thereby informing both practical implementation and theoretical implications. Qualitative data will be analyzed thematically using NVivo 14 software to support and manage the analytic process (74).

*a priori* sample size calculations with G-Power (75) suggested that a sample of 580 participants would be sufficient to detect a moderate effect size (*d* = 0.3), assuming a two-group design, 80% power, and an alpha of.05.

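### The linear mixed model sentence reads as a contrast of change from baseline; stating a baseline-adjusted 12-week difference would give more precision at no cost

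*Protocol article*

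**What the plan says.** Section 2.7 of the Protocol article gives the between-arm analysis in one sentence: "To examine between-group differences in continuous outcome measures from baseline to the 12-week follow-up, a linear mixed model (LMM) will be applied". The model deals with nesting by "incorporating random intercepts to account for intra-class correlation and hierarchical clustering effects". It is also credited with a missing-data advantage: "LMMs handle missing data robustly under the assumption of missing at random". Change within each arm is handled separately: "Within-group changes will be assessed using dependent *t*-tests". The section lists no fixed effects. It does not say whether baseline is a covariate, a first outcome record with free arm means, or a first record with a common mean.

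Section 2.6.2 lists the outcomes concerned. Ten of its twelve entries are taken at both occasions; aerobic fitness, for example, is "Measured with the YMCA 3-min step test (60) at baseline and 12-week follow-up". The other two (attention and concentration, heart rate) are taken only around a mid-intervention session. All are secondary. The primary outcomes in section 2.6.1 are adherence to the breaks and the experiences of students and teachers.

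**The concern.** The sentence describes how the arms differ in their movement from baseline, not how they differ at 12 weeks given baseline. Two neighbouring statements point the same way. With only two occasions, the missing-at-random advantage of a mixed model matters mainly when baseline and week 12 are both outcome records. The paired t-tests also make change the reporting frame. An analyst who followed the text would ordinarily fit arm, time and arm-by-time.

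Under randomisation the arms share the same expected baseline. A change contrast subtracts the whole observed baseline difference, although only the part that predicts follow-up should be removed. Two things are at stake. Precision is lost on the less repeatable measures, in a trial with 519 consenting students against a stated target of 580. And when one arm happens to start worse, the estimate tilts in that arm's favour.

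**Working it through.** **The plan's own figure.** The article gives no figure for this contrast. Its only calculation is 580 students for d = 0.3, two groups, 80% power and alpha 0.05. Per arm, n = 2(1.96 + 0.84)²/0.3², which gives 175, so 350 in total. That does not reproduce 580. Two-sided 95% power gives 578 (580 by the t-test). This mismatch is a separate matter; only d = 0.3 is used below, as a yardstick.

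**Inputs from the article.** 519 consenting students; 1:1 allocation; 12 academic classes (four at each of three schools); about 300 vocational students in classes of 12 to 17. The last gives 300/17 to 300/12, about 18 to 25 classes, so about 30 to 37 in all. With 36 classes the mean size is 519/36 = 14.4.

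**Assumed inputs.** The correlation r, the ICC and the class-by-time variance.

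**Step 1: precision, independent students.** Relative to σ², the change contrast has variance factor 2(1−r) and the adjusted contrast 1−r². Their ratio, adjusted to change, is (1+r)/2.

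| r | change | adjusted | ratio |
|---|---|---|---|
| 0.5 | 1.00 | 0.75 | 0.75 |
| 0.7 | 0.60 | 0.51 | 0.85 |
| 0.9 | 0.20 | 0.19 | 0.95 |

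**Step 2: precision, clustered students.** Simulation with 34 classes of 15, adjusting for the student's baseline only:

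| student r | class r | ICC | SD change | SD adjusted | variance reduction |
|---|---|---|---|---|---|
| 0.5 | 0.5 | 0.05 | 0.1167 | 0.1011 | 1 − (0.1011/0.1167)² = 25% |
| 0.7 | 0.7 | 0.05 | 0.0901 | 0.0835 | 14% |
| 0.7 | 0.9 | 0.05 | 0.0761 | 0.0722 | 10% |
| 0.5 | 0.8 | 0.10 | 0.1082 | 0.1030 | 9% |
| 0.7 | 0.9 | 0.10 | 0.0807 | 0.0796 | 3% |

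Both estimators were centred on the true value. A second simulation (36 classes, 516 students, ICC 0.05) gave, for r = 0.5 to 0.7, reductions of 5–8% with no class-by-time variance, 12–17% with class-by-time variance 0.02 and 17–19% with 0.05. At r = 0.9 the reduction was nil. The range is therefore about nil to 25%.

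**Step 3: likely size of chance imbalance.** The SD of the baseline arm difference is √(4·DE/519), with design effect DE = 1 + (14.4 − 1)·ICC. For ICC 0.05, 0.10 and 0.20, DE is 1.67, 2.34 and 3.68, and the SD is 0.113, 0.134 and 0.168. An imbalance of 0.15 SD is thus unremarkable if allocation were unrestricted.

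**Step 4: effect of that imbalance.** Let β be the slope of the follow-up arm difference on the baseline arm difference. Given imbalance B, the change estimate is off by −(1−β)B. With clusters of size m,

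β = (m·cov_class + cov_student)/(m·var_class + var_student).

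For total r = 0.5 and B = 0.15:

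- Class-level correlation also 0.5: β = 0.5, shift 0.5 × 0.15 = 0.075 SD.
- Stable class effects, ICC 0.05: β = (0.72 + 0.45)/(0.72 + 0.95) = 1.17/1.67 = 0.70, shift 0.30 × 0.15 = 0.045 SD.
- Stable class effects, ICC 0.20: β = (2.88 + 0.30)/(2.88 + 0.80) = 3.18/3.68 = 0.86, shift 0.14 × 0.15 = about 0.02 SD.

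In the 34-class simulation, the slope of the change estimate on imbalance was −0.51 and −0.30 in the first two rows of the table; student-level adjustment brought it to −0.01 and 0.00. In the last row it was −0.16 for change and +0.12 for student-level adjustment. That remainder is why the class-mean baseline belongs in the covariate form.

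**The case against.** The strongest reply is that the article does not fix the choice criticised. It gives no fixed effects, and a mixed model with arm means held equal at baseline could be described by the same sentence. The exact terms are commonly left to a full protocol or analysis plan, and neither is shown. This stands as far as it goes: a reader might infer that the plan adopts free baseline means and rejects adjustment, and the text does not support that. What remains is that the sentence does state a contrast, that its natural reading is change, and that a better contrast is available from data already collected.

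Four other tempting readings also fail.

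- *The result would be biased.* It would not. The error depends on the realised imbalance and averages to zero over randomisations.
- *The loss amounts to a third of the sample.* The figure 1/0.75 = 1.33 at r = 0.5 treats students as independent, and they are nested in classes.
- *High clustering makes the imbalance error worse.* A larger ICC enlarges the imbalance but, if class effects are stable, reduces the part wrongly subtracted (0.02 against 0.045 SD above).
- *So few classes make serious imbalance likely.* There are about 30 to 37, drawn within schools, with vocational classes stratified by gender, size and subject area. Both features can bring the imbalance below the Step 3 values.

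**Conclusion.** The point holds as a recommended improvement, not as an error that invalidates the analysis. Read naturally, section 2.7 plans a change contrast that is valid but gives up precision: 5% to 25% of the variance for independent students at r from 0.9 to 0.5, and about nil to 25% under clustering. A chance imbalance of 0.15 SD at r = 0.5 would move an estimate by about 0.02 to 0.075 SD, at most a quarter of the d = 0.3 in the sample size statement. Every r, ICC and class-by-time variance here is assumed. The gain is largest for measures with low repeatability and almost disappears when r is near 0.9 or class differences are very stable. It concerns secondary outcomes of a pilot and leaves the primary adherence and focus-group evaluation untouched.

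**What to change.** Add one sentence to section 2.7: for each continuous secondary outcome measured at baseline and 12 weeks, the effect is the between-arm difference at 12 weeks adjusted for baseline. Then name one of two forms:

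- a 12-week outcome model with the student's baseline value and the class-mean baseline as covariates; or
- the two-record mixed model with arm means constrained equal at baseline (time plus arm-by-time, no arm main effect).

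The second form fits the missing-data reasoning already in the article, because it keeps students with only one of the two occasions. The cost is a line of wording. No new data, visits or students are needed. If a fuller analysis plan already specifies one of these, the article's sentence need only say so.
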